## Abstract

**Introduction:**

Asthma and its associated exacerbation are heterogeneous. Although severe asthma attacks are systematically prescribed corticosteroids and often antibiotics, little is known about the variability of response to these therapies. Blood eosinophils and fractional exhaled nitric oxide (FeNO) are type 2 inflammation biomarkers that have established mechanistic, prognostic and theragnostic values in chronic asthma, but their utility in acute asthma is unclear. We speculate that the clinical and biological response to those treatments varies according to inflammometry and microbiological test results.

**Methods and analysis:**

An observational longitudinal pilot study with multimodal clinical and translational assessments will be performed on 50 physician-diagnosed ≥12-year-old asthmatics presenting with an asthma attack and 12 healthy controls, including blood eosinophil count (venous and point-of-care (POC) capillary blood), FeNO and testing for airway infection (sputum cultures and POC nasopharyngeal swabs). People with asthma will be assessed on day 0 and after a 7-day corticosteroid course, with home monitoring performed in between. The primary analysis will be the change in the forced expiratory volume in 1 s according to type 2 inflammatory status (blood eosinophils ≥0.15×10^9^/L and/or FeNO ≥25 ppb) after treatment. Key secondary analyses will compare changes in symptom scores and the proportion of patients achieving a minimal clinically important difference. Exploratory analyses will assess the relationship between clinical, lung function, inflammatory and microbiome parameters; satisfaction plus reliability indices of POC tests; and sex–gender variability in treatment response. Ultimately, this pilot study will serve to plan a larger trial comparing the clinical and biological response to systemic corticosteroids according to inflammatory biomarkers, offering valuable guidance for more personalised therapeutic strategies in asthma attacks.

**Ethics and dissemination:**

The protocol has been approved by the Research Ethics Committee of the CIUSSS de l'Estrie–CHUS, Sherbrooke, Quebec, Canada (#2023-4687). Results will be communicated in an international meeting and submitted to a peer-reviewed journal.

**Trial registration number:**

ClinicalTrials.gov Registry (NCT05870215).

WHAT IS ALREADY KNOWN ON THIS TOPICAsthma exacerbations pose a substantial burden on healthcare systems and individuals. Despite existing knowledge, there are still gaps in our understanding of the precise mechanisms underlying asthma exacerbations, the role of biomarkers and the potential for more personalised treatment approaches.WHAT THIS STUDY ADDSPhenotyping the Responses to Systemic Corticosteroids in the Management of Asthma Attacks (PRISMA) is an observational longitudinal pilot study with multimodal clinical and translational assessments that aims to stratify the clinical and biological responses to systemic corticosteroids in asthma attacks according to type 2 inflammatory biomarkers (blood eosinophils and fractional exhaled nitric oxide) and will explore the relationship between other clinical, inflammatory biomarkers/proteins, and microbiological parameters and treatment response.HOW THIS STUDY MIGHT AFFECT RESEARCH, PRACTICE OR POLICYBy conducting an extensive array of clinical and translational assessments, this study aims to provide a holistic view of asthma attacks, shedding light on their multifaceted nature and paving the way for a comprehensive, larger-scale clinical trial.

## Introduction

Asthma is a prevalent chronic respiratory disease affecting over 400 million people worldwide.^1^ Asthma attacks are loosely defined as deterioration of symptoms and/or lung function from baseline.^2^ In contrast, the more stringent classification of attack severity is based on treatment decisions: a severe episode requiring emergency room consultation and/or ≥3 days of oral corticosteroids (OCs) and/or hospitalisation.^3^ Severe asthma attacks cause morbidity, healthcare utilisation and avoidable deaths.^4^ Attacks are ‘red flags’^5^: a sentinel event and an opportunity for personalised asthma management.^6^ Despite growing evidence of heterogeneity of mechanisms driving asthma attacks, the standard of care in acute asthma has not changed for 30 years. It consists of a ‘one-size-fits-all’ treatment with OCs and often antibiotics.^7 8^

In stable severe asthma, the treatment paradigm is evolving towards targeting treatable traits^9^—a revolution launched after heterogeneity of stable severe asthma was established clinically^10^ and translationally.^11–13^ An important aspect of this paradigm is to guide therapeutic decisions based on clinical characteristics that predict greater treatment response. The most noteworthy application is the targeted use of anti-inflammatory medications in asthma characterised by a type 2 inflammatory phenotype, identified in the clinic using simple tests such as blood eosinophil count (BEC) and fractional exhaled nitric oxide (FeNO).^6 14^

BEC and FeNO are effective biomarkers for several reasons. First, they provide complementary mechanistic information on different immune compartments involved in the pathogenesis of asthma. Blood eosinophilia is predominantly caused by circulating interleukin (IL)-5 activity and reflects the systemic component of type 2 inflammation,^15 16^ whereas FeNO elevation reflects the airway epithelial component mediated by IL-13-mediated inducible nitric oxide synthase.^16–18^ Second, they have additive and independent value in predicting severe asthma attacks in control arm trial populations across mild,^19^ moderate^20^ and severe asthma.^21–23^ Third, BEC and FeNO predict treatment response: raised levels are associated with greater benefit from anti-inflammatory therapies in chronic asthma, be it low-dose inhaled corticosteroids in mild disease,^19^ higher-dose inhaled corticosteroids in moderate^20 24^ or type 2 targeted biologics in moderate-to-severe asthma.^25–27^ Importantly, these biomarkers are simple, non-invasive and accessible.^14^ Just as high blood pressure and cholesterol levels are regularly assessed to predict and prevent heart attacks, BEC and FeNO are emerging as airway equivalents to quantify the modifiable risk of asthma attacks.^23 27 28^

The critical remaining questions are (a) how airway signalling (reflected by FeNO) and an increased systemic eosinophil pool (reflected by BEC) relate to the underlying biological pathways that contribute to asthma exacerbation and (b) how the type 2 inflammatory phenotype impacts the response to acute anti-inflammatory corticosteroid treatment. An often-cited confounder is airway infection, which is difficult to diagnose when relying on conventional sputum cultures but can indicate either greater susceptibility to macrolide antibiotics^29 30^ or, conversely, can decrease the use of antibiotics (when a viral infection is diagnosed and/or no bacterial infection is identified).^31^

In acute asthma, several studies have documented the heterogeneity of attacks,^32–39^ with the presence of sputum inflammation characterised by elevated eosinophils^32 33 36–38^ or neutrophils.^34–38^ Importantly, these inflammatory phenotypes are indistinguishable from the point of view of initial symptoms or lung function.^38^ Other features are high BEC and elevated FeNO,^37^ increased levels of IL-8 in sputum^35 36^ or serum C reactive protein (CRP)^37^ or a different microbial flora related to FeNO values.^39^ However, treatment responses to acute systemic corticosteroid and antibiotic courses have not been related to the type 2 inflammatory phenotype and the presence of airway infection, respectively.

Concerning point-of-care (POC) measurements, it is noteworthy that capillary POC-BEC has been successfully studied in chronic airway diseases^40 41^ but not in asthma attacks; they are also approved by Health Canada and the US Food and Drug Administration (FDA).^40^ Furthermore, POC-FeNO technologies also exist, have been used for remote monitoring of FeNO, and are approved for use by Health Canada and the FDA.^41^

Finally, following the COVID-19 pandemic, we have increasing evidence supporting the relevance of early knowledge of viral and/or bacterial infection. Brendish *et al* previously showed that antibiotic use in acute airway disease dropped only once the physician had the results from the POC test, thus highlighting the importance of immediate notification of rapid multiplex testing.^31^ Improving the accessibility and affordability of POC inflammometry and microbiology testing in asthma is very likely to improve the situation for patients, physicians, manufacturers and pharmaceutical companies because it will optimise the management of the patients, identify those with type 2-driven worsening of the disease giving them better access to targeting medications and avoiding unnecessary antibiotics.^42^

The treatable trait success story of chronic asthma certainly makes a case for the reappraisal of our approach to acute asthma.^6 7 43^ Is it time for precision medicine to attack the problem of asthma attacks? A worthwhile question, considering that corticosteroid toxicities appear after the lifetime equivalent of only four bursts (≥1000 mg cumulative dose) of prednisone—that is, four severe asthma attacks^44^—and the increasing levels of resistance to antibiotics observed, mainly due to inadequate prescriptions.^7 29^ Biomarker-guided management could avoid harm to individual patients and society stemming from the inappropriate use of OCs and/or antibiotics due to overuse or without proper consideration of their potential risks and side effects.^44 45^ Simply stated, corticosteroid and antibiotic stewardship can and should be assisted by acute POC testing.

Based on previous knowledge from chronic stable asthma and reports that asthma attacks are heterogeneous events, we hypothesise that treatment responses to OCs in acute asthma vary according to the underlying inflammatory phenotype. Specifically, we speculate that events identified by raised BEC and/or FeNO benefit most from OCs and that events presenting with low type 2 biomarkers have a lesser objective clinical and biological anti-inflammatory response but perhaps higher rates of airway infection or dysfunction. If this proves to be the case, we will be in a solid position to move forward with a randomised clinical trial comparing biomarker-directed OC use with the current ‘one-size-fits-all’ approach. An important secondary hypothesis of our study is that POC inflammatory and microbiological assessments in acute asthma are possible, acceptable and reliable. The ramifications of such findings would be to plan a clinical trial assessing biomarker-guided asthma attack management in primary care.

## Methods and analysis

### Study design

We planned an observational longitudinal pilot study with before/after multimodal assessments plus home monitoring (figure 1). The study will be mainly conducted at the Centre Hospitalier Universitaire de Sherbrooke’s research centre, with a secondary site to open at the Institut Universitaire de Pneumologie et Cardiologique de Québec (Québec, Canada) if needed for recruitment purposes. This is not a clinical trial; OCs are the standard treatment for asthma attacks and will be administered as required.

**Figure 1 F1:**
[figure not shown]
Study design, methods overview and expected impacts of the PRISMA asthma attack pilot study. Our hypothesis is that asthma attacks are heterogeneous events to which objective treatment responses following systemic corticosteroids vary according to the underlying inflammatory phenotype. *Healthy controls do only visit 1. #Concomitant antibiotic use will only be considered if: C reactive protein (CRP) >20 mg/L, procalcitonin (PCT) >0.25 µg/L or positive sputum to a significant bacterial pathogen. †Refers to the text for a full list of exploratory outcomes. ACQ-5, five-item Asthma Control Questionnaire; COPD, chronic obstructive pulmonary disease; Eos, eosinophil; FeNO, fractional exhaled nitric oxide; FEV_1_, forced expiratory volume in 1 s; NELF, nasal epithelial lining fluid; NP, nasopharyngeal; od, once daily; po, orally; POC, point-of-care; PRISMA, Phenotyping the Responses to Systemic Corticosteroids in the Management of Asthma Attacks; qPCR, quantitative PCR.

### Participants

People ≥12 years old with physician-diagnosed asthma since >6 months experiencing an asthma attack as defined by GINA (episode characterised by a progressive increase in symptoms of shortness of breath, cough, wheezing or chest tightness that represent a change from the patient’s usual status)^2^ with a patient and/or physician decision to initiate a burst of OCs (but not yet started) will be assessed within 24 hours on weekdays after a screening telephone call. Exclusion criteria are a SARS-CoV-2-positive event, asthma treated with a monoclonal antibody or maintenance OCs, current smoking, significant overlapping cardiopulmonary disease (including chronic obstructive pulmonary disease, defined as age >40 years old AND persistent airflow limitation with forced expiratory volume in 1 s (FEV_1_)/forced vital capacity <0.7 AND >10 pack-year smoking history or α-1-antitrypsin deficiency), a confounding immunological state, ongoing pregnancy or contraindication to corticosteroids.

Although we will assess asthmatics with a history of physician-diagnosed asthma, patients included in the primary analysis and counting toward the target sample size will need to have objective proof of asthma as defined by international guidelines^2^ either based on the medical record or with a clinically required follow-up test ordered by the study respirologist and performed after study participation. Unconfirmed asthmatics data will be reported but not used for the primary analysis.

Non-atopic, non-smoking healthy volunteers with normal spirometry and no history of lung disease will form the control cohort. All participants (±their parent or legal tutor) must provide informed consent for the study protocol. Patients who cannot or refuse to participate in the diary card data collection for the home monitoring period will still be able to participate in all other study procedures.

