Visual Analogue Scale of asthma symptoms (6 items)		x		x	
Pittsburgh Vocal Cord Dysfunction Index		x		x	
Nijmegen Questionnaire		x		x	
Hospital Anxiety and Depression Scale		x		x	
Survey of % of home tests monitored				x	
Satisfaction questionnaire about point-of-care biomarker measurements: participant				x	
Satisfaction questionnaire about point-of-care biomarker measurements: letter and email sent to treating doctor				x	
Respiratory physiology					
FeNO measurement (NIOX)		x		X	
Teaching of FeNO measurement		x			
FeNO measurement		x	x	x	
Teaching of peak expiratory flow measurement		x			
DEP measurement		x	x	x	
Capillary blood eosinophils: sight OLO measurement		x		x	
Force spirometry—pre-bronchodilator		x		x	
Forced oscillation—pre-bronchodilator					
Salbutamol 400 µg		x		x	
Force spirometry—post-bronchodilator		x		x	
Forced oscillation—post-bronchodilator					
Inflammometry					
Hospital viral multiplex PCR (BIOFIRE on nasopharyngeal swab)		x		x	
Nasosorption		x		x	
Nasal cytology brushes		x		x	
Induced or spontaneous sputum collection for differential cell count+supernatant, plugs and cell pellet for biobank		x		x	
Induced or spontaneous sputum collection for hospital microbiology analysis		x		x	
Hospital blood tests (1 EDTA tube, 1 heparin tube): complete blood count with differential, C reactive protein		x		x	
Allergy testing (hospital blood tests; 1 tube) for total serum IgE, specific serum IgE: grass mix, weed mix, tree mix, mould mix, house dust mites *Dermatophagoides pteronyssinus* and *D. farinae*, *Aspergillus fumigatus*		x			
Research laboratory blood tests: 1 EDTA, 4 heparin, 2 serum, 1 whole blood for research laboratory (biobank)		x		x	
Chest X-ray		x			
Urine sample; urine creatinine for hospital; sample frozen for research laboratory (biobank)		x		x	

FeNO, fractional exhaled nitric oxide.

Visit 2 will additionally include a survey of adverse events relating to corticosteroids, patient satisfaction questionnaires and permission to contact the patient’s primary care provider for a physician survey about POC testing.

Visit 3 is a web-based survey reviewing the number of subsequent exacerbations, medication changes and ACQ-5 score and allowing the patient to prompt a call from the study team (or vice-versa if the study team has a test to follow up on).

All study visits will occur in the morning to avoid the confounding effect of circadian variation of type 2 inflammatory biomarkers.^51–53^

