### Follow-up visit

Ninety days after visit 2, patients will be contacted by email to complete an internet form containing ACQ-5, peak flow measurement and questions about asthma management.

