### Outcome measures

#### Primary outcome

Change in the FEV_1_ between visits, with particular emphasis on a comparison based on the presence or absence of type 2 inflammatory events within the patient cohort. Specifically, we will classify type 2 high events on the basis of visit 1 BEC ≥0.15×10^9^ cells/L and/or FeNO ≥25 ppb.

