#### Secondary outcomes

Change in ACQ-5 between visits according to type 2 inflammatory status.The proportion of patients who achieve a minimal clinically important difference (MCID) ≥10% for FEV_1_ and ≥0.5 points for ACQ-5, according to the presence of type 2 high or type 2 low events.^58^ The magnitude of response will be rated as poor, moderate or good if the change is <1×, ≥1× or ≥2× the MCID values, respectively.

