### Statistical analyses

Descriptive statistics will be presented for the complete sample and separated by groups (ie, frequencies and percentages for categorical, mean, and SD or median and IQR based on the distribution). The normality of variables will be assessed visually using Q–Q plots and histograms. Demographics will be compared between asthmatics and healthy controls using unpaired Student’s t-tests (Mann-Whitney) for continuous variables and Χ^2^ (Fisher’s exact test) for categorical variables. Due to the small sample size, no imputation methods are planned a priori for missing data. Frequencies and percentages of missing will be presented, and listwise deletion will be used for concerned analyses.

We will employ an unpaired two-sample t-test (Mann-Whitney U test if non-parametric) to assess the change in FEV_1_ (primary outcome) and ACQ-5 (key secondary outcome) between visits 1 and 2 according to type 2 inflammatory status. Additionally, to assess whether the observed change in FEV_1_ within subgroups defined by type 2 high events is clinically meaningful, we will employ a Χ^2^ test to compare the proportion of patients achieving the MCID between the two groups, using an MCID of 10% relative change in FEV_1_ and 0.5 points in ACQ-5. Finally, the above results will allow for a power calculation to plan a randomised controlled trial on key outcomes.

Exploratory analyses will include an association of the outcome measures with type 2 inflammatory mediators at visit 1 using further multivariable models. To consider the influence of potentially confounding variables, simple and multiple linear regression models will be performed for both independent variables (BEC and FeNO). Covariates considered are age, sex at birth, body mass index, atopic status, serum IgE, Asian race, nasal polyposis,^21^ smoking history, Charlson index, treatment intensity at baseline, exacerbation history in the past 12 months and ACQ-5. Only confounders associated (p<0.1) with FEV_1_ will be included in the final multivariable model. A linear mixed-effects analysis of the longitudinal improvements in parameters measured at home (FeNO, peak expiratory flows and symptom scores) according to baseline FeNO and BEC.

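### FEV1 response is judged without reference to the patient's usual FEV1, so full recovery from a small fall is rated 'poor' and a shallower attack cannot be told from a lesser corticosteroid response

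*Protocol article*

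**What the plan says.** All references are to the protocol article.

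- **Entry (Participants).** An attack is a "progressive increase in symptoms of shortness of breath, cough, wheezing or chest tightness that represent a change from the patient’s usual status", together with a patient or physician decision to begin oral corticosteroids. The Introduction's general definition is wider: "Asthma attacks are loosely defined as deterioration of symptoms and/or lung function from baseline". Neither makes a fall in lung function a condition of entry.
- **Primary outcome.** Change in FEV1 "between visits, with particular emphasis on a comparison based on the presence or absence of type 2 inflammatory events within the patient cohort". Statistical analyses assigns this an unadjusted two-sample t-test, or Mann-Whitney.
- **Rating (Secondary outcomes).** "The magnitude of response will be rated as poor, moderate or good if the change is <1×, ≥1× or ≥2× the MCID values, respectively". Statistical analyses fixes the FEV1 scale: "using an MCID of 10% relative change in FEV"1. The ACQ-5 MCID is 0.5 points.
- **Spirometry (Table 1).** The row "Force spirometry—pre-bronchodilator" has two ticks, read as day 0 and day 7. Home monitoring uses peak flow. The day-97 contact is remote: "patients will be contacted by email to complete an internet form containing ACQ-5, peak flow measurement and questions about asthma management"; spirometry is not part of it.
- **Covariates (Statistical analyses).** The list for the exploratory models contains neither usual FEV1 nor visit 1 FEV1.
- **Earlier or later lung function (Participants).** Asthma is confirmed "either based on the medical record or with a clinically required follow-up test ordered by the study respirologist", the test being done after participation. Its only stated use is to confirm the diagnosis.

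**The concern.** FEV1 regained over seven days is the product of two things: how far FEV1 fell in the attack, and what share of that fall came back. The plan measures the product and interprets it as response. With no reference to usual FEV1, two consequences follow.

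First, the poor/moderate/good rating can place a half-recovered patient above a fully recovered one.

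Second, if type 2-low attacks take less FEV1 away, that group will show a smaller change even when both groups regain the same share. The study could not then separate a smaller fall from a lesser effect of corticosteroids. Because these results are meant to feed the power calculation for a randomised trial, the ambiguity would carry forward.

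**Working it through.** **1. The plan's own figure.** Sample size assumes a difference of 10%, SD 10%, 1:1 allocation, two-sided α 0.05 and 90% power. The normal approximation gives 22 per group (44). The t-test gives 22.02, rounded up to 23 per group, or 46 in total, with power 0.912 (0.934 at 25 per group). The stated n=46 reproduces and is not affected by this point.

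**2. The rating rule (no assumptions).** Let U be usual FEV1, f the fraction lost in the attack and r the share of the loss regained by visit 2.

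- Visit 1 FEV1 = U(1 − f). Visit 2 FEV1 = U(1 − f) + r·f·U.
- Relative change = r·f/(1 − f).
- Full recovery (r = 1) stays below 10% when f < 0.10/1.10 = 9.1%, and reaches 20% when f ≥ 0.20/1.20 = 16.7%.
- Half recovery (r = 0.5) reaches 10% only when f ≥ 16.7%.

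| Fall from usual | Share regained | Relative change | Rating |
|---|---|---|---|
| 5% | all | 5/95 = +5.3% | poor |
| 8% | all | 8/92 = +8.7% | poor |
| 12% | all | 12/88 = +13.6% | moderate |
| 20% | half | 10/80 = +12.5% | moderate |
| 20% | all | 20/80 = +25% | good |

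**3. The group comparison (all inputs below are assumed).** 25 per group; usual FEV1 85 ± 18% predicted; SD of the fall 8 points; both groups regain 70 ± 15% of the fall; measurement error 2 points; error of the record's usual FEV1 3 points; 1,500 runs. FEV1 change, in points of % predicted, is regressed on type 2 group. There is no difference in share regained, so a significant result reflects depth alone. For falls of 20 versus 10, the expected unadjusted difference is about 0.7 × 10 = 7 points, slightly less because a fall cannot be negative.

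| Mean falls (points) | Unadjusted | + visit 1 FEV1 | + visit 1 and usual FEV1 |
|---|---|---|---|
| 20 vs 10 | 6.7 points, 94% significant | 5.6 points, 85% | 0.6–0.7 points, 7–8% |
| 20 vs 15 | 43% | 33% | 5.5% |

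With equal falls of 15 points there is no inflation, and the standard error drops from 1.9 to 1.1 points when both covariates are added. Visit 1 FEV1 alone corrects little, because it mixes long-standing level with acute loss.

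**4. A second set of assumptions.** SD of the fall 6 points, 80 ± 20% regained in both groups, measurement SD 5%, 25 per group, outcome as relative change.

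| Mean falls | Mean changes | t-test rejects |
|---|---|---|
| 15% vs 15% | 14.6% vs 14.6% | 5% |
| 15% vs 10% | 14.6% vs 9.4% | 54% |
| 20% vs 12% | 20.6% vs 11.4% | 91% |

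The last row is a difference of 9.2 points, close to the 10 points the study is sized to detect. Responders at the 10% MCID are 85% versus 54%.

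**5. How far the correction depends on the record value.** Model of step 3, falls of 20 versus 10, both covariates, changing only the error of the record's FEV1:

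| Record error (points) | Residual difference | Significant |
|---|---|---|
| 3 | 0.6–0.7 | 7–8% |
| 6 | 2.3 | 31% |
| 8 | 2.9 | 44% |
| 10 | 3.6 | 55% |

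The gain in precision shrinks too: at 8–10 points the standard error is about 1.5 instead of 1.1.

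**The case against.** **Absolute FEV1 gain is a legitimate target.** The hypothesis is that raised-biomarker events benefit most. A group with little FEV1 to regain does have less FEV1 benefit, and if type 2 inflammation causes the deeper fall, depth lies on the causal pathway. This stands. It is why the primary test need not change and why the adjusted analysis answers a different question.

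**Differential depth is not shown.** A reader might infer that the primary comparison is biased. The documents do not support that. The Introduction says only that type 2-low events perhaps have more airway infection or dysfunction, and gives no figure for FEV1 loss. Its statement that phenotypes look alike in initial lung function does not settle the matter either way, since it concerns level at presentation and not the fall from usual. What remains is that the stated plan could not check.

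**The article is condensed.** A reader might infer that no usual FEV1 will ever be available. That goes too far: the medical record is consulted and may hold one, and the full protocol may capture it. But the article does state the outcome, test, covariates and rating, and none uses such a value.

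**The rating's reach is limited.** It is secondary, described as exploratory, and also applied to ACQ-5, so symptom-driven attacks are judged on symptoms as well. Spirometry before and after bronchodilator gives partial information on reversible loss. Both are fair, but neither repairs the FEV1 rating.

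**FEV1 is already named as a pitfall.** The Discussion does so for another reason: type 2 inflammation has not always been linked with FEV1.

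**Conclusion.** The point holds in two parts of different strength.

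The rating flaw is certain. Under the stated rule, complete recovery from a fall under 9.1% is 'poor' and half recovery from a 20% fall is 'moderate', whether or not depth differs by type 2 status.

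The ambiguity in the group comparison is conditional on attack depth differing by type 2 status. If it does, the effect can be large: 94% spurious significance at assumed falls of 20 versus 10 points, 43% at 20 versus 15, and none when falls are equal. These percentages illustrate the assumed scenarios; they do not estimate this study's error rate.

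A reader might also infer that adjusting for a chart FEV1 removes the problem. It does so nearly only when that value is accurate to about 3 points. At 6–8 points, 31–44% of runs remain significant, so an adjusted result would still need cautious reading.

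**What to change.** 1. Keep the primary outcome, the primary test and the sample size.
2. Where the medical record used to confirm asthma holds a stable pre-attack FEV1, abstract the most recent one with its date.
3. Pre-specify a supporting analysis of FEV1 change by type 2 status, adjusted for visit 1 FEV1 and usual FEV1. Label it as addressing the share of loss regained, a different question from absolute FEV1 gain.
4. In the FEV1 rating, show patients whose visit 1 FEV1 was already within about 9% of usual as a separate category, not as 'poor'.
5. Report how many patients have a usable value and how old it is. State that the analysis rests on that subset and corrects only partly when values are old or noisy.
6. Do not pool spirometry from the post-participation follow-up test with pre-attack values. It is post-treatment and may itself reflect response, so use it, where available, only in a labelled sensitivity analysis.

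The cost is one chart-abstracted value with its date, one supporting model and one extra display category. No visit or procedure is added. The drawback is a possibly small and selected subset with a usable record value.
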